#### Primary outcome

The primary outcome is the changes in number of prescribed drugs in patients older than 65 years between the baseline and follow-up period.

This outcome refers to standard 2.2 in the DHQP: physicians in the practice have knowledge about the basic list for rational pharmacotherapy. The practice conducts, according to medical judgments, annual controls in patients with chronic disease, comprising assessment of prescriptions.

The primary outcome is selected because inappropriate use of many concurrent drugs, especially in older people, imposes a substantial burden of adverse drug events, ill health, disability, hospitalization and even death. The single most important predictor of inappropriate prescribing adverse drug events (ADEs) in older patients is the number of prescribed drugs [15]. One report estimated the risk of ADE as 13% for two drugs, 38% for four drugs and 82% for seven drugs or more [15]. A Danish study from 2000 showed that among 75-year-old persons living at home, 60% used three or more prescribed drugs and 34% used five or more [16]. A more recent study performed by the pharmacist foundation found that almost 40% of the elderly older than 65 years use six or more drugs, while this is the case for more than 50% of the elderly older than 80 years [17]. National guidelines for general practice recommend critical reviews of the elderly patients’ medication [18], and secure medication in elderly patients relates to all four areas in DHQP.

It is not possible to assess whether the medication given to the individual patient is reasonable, as we have no access to the patients’ diagnosis or the indication. Therefore, we will analyse any changes in number of drugs in elderly persons (older than 65) for accredited practices and non-accredited practices.

Our main hypothesis is that implementing DHQP will decrease the number of prescribed drugs during the accreditation scheme.

#### Secondary outcomes

The secondary outcomes focus on safe medication practices, good clinical practices and quality and patient safety according to the DHQP. These outcomes relate directly to one of the standards concerning critical patient safety issues (standard 2.2), and they are expressed as changes in amounts or prevalence between the observation period and the baseline period.

The rationale for each of the secondary outcomes is presented in Table 2.

##### Safe medication

Safe medication use includes:Changes in the proportion of polypharmacy (>5 prescribed drugs) patients older than 65 yearsChanges in daily drug dose (DDD) of non-steroidal anti-inflammatory drugs (NSAIDs) without proton pump inhibitor (PPI)Changes in DDD of sleeping medicine.

##### Good clinical practice

Good clinical practice includes:Changes in the proportion of elderly persons older than 75 receiving a preventive home visit (PHV)Changes in the number of annual controls for chronic disease (ACCD) between periodsChanges in the number of spirometries performedQuality and patient safety:Changes in proportion of practices with a reported adverse event (RAE)Changes in proportion of practices with a patient satisfaction survey between periods.

##### Mortality

Mortality is evaluated as changes in mortality rates between periods.

### Data collecting periods

All outcomes except mortality are surveyed in the following two periods:Baseline data are collected from 1 January 2014 to 30 June 2014.Follow-up data are collected from 1 January 2017 to 30 June 2017.

For mortality the periods are:Baseline data are collected from 30 June2014 to 31 August 2014.Follow-up data are collected from 30 June 2017 to 31 August 2017.

### Data sources

Data on clinical effects measures are prospectively collected and stored within various national registers. However, the project group does not have permission to retrieve data until autumn 2017. Prescription data from 2015 formed the basis for the power analysis. Because of the CRS, these data can be linked to the patients’ civil registration number and analysed within a common research database hosted by Statistics Denmark (StatDen) and Statens Serum Institut (SSI). A named responsible statistician will obtain permission to work with data within the frames of StatDen.

We will use the National Prescription Register (NPR), which is a database that includes records of all prescriptions dispensed at all Danish community pharmacies since 1995 (information on drugs administered to hospital inpatients is not registered) to calculate the number of drugs per patients based on the date a prescription is redeemed, the pharmaceutical group (ATC code 4) and the DDD in the redeemed prescription. Based on this information, we will calculate the number of pharmaceutical groups through which an individual redeemed prescriptions on 30 June in the years 2014 and 2017.

The Danish Register of Causes of Death (DRCD), which includes information on specific causes of death based on death certificates, will be used to define all-cause mortality.

GP and practice characteristics and services provided (e.g. spirometry and annual check-ups for chronic conditions) will be retrieved from the Danish National Health Services Register (DNHSR).

All baseline data are available in the mentioned registers/databases and will be retrieved starting from autumn 2017.

### Statistics

Differences in baseline characteristics are reported as numbers (percentages) and tested using chi-squared tests.

Linear regression will be used for continuously valued outcomes (e.g. number of different drugs, safe medication, annual controls, etc.) and logistic regression for binary outcomes (polypharmacy, preventive home visits, changes in proportion of practices with reported adverse events and changes in proportion of practices with a patient satisfaction survey). Analyses will account for clustering of patients in practices by generalized estimating equations (GEE). A level of 5% will be taken as statistically significant.

Analyses will be performed in SAS version 9.4 (SAS Institute, Cary, NC, USA).

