### Randomization

IKAS decided that surveys in all five regions of Denmark should be evenly distributed for the 3 years during which the accreditation process takes place. Moreover, it was decided by IKAS that the accreditation should be conducted by means of municipalities (each Danish region is divided into several smaller municipalities) and that the order of municipalities should be completely random.

Time for accreditation of the practices in the 98 municipalities in Denmark was determined in a randomized lots drawing conducted on 22 September 2014 by IKAS, and provided the basis for a prospective study. Two impartial persons from IKAS conducted the drawing. Within each of the five Danish regions, one-third of the practices within the municipalities that were drawn first were allocated to accreditation in 2016, the next third to 2017 and the last third to 2018. If large municipalities were drawn and this resulted in an excess of practices greater than one-third of the practices in a region, the practices were split over 2 allocation years based on the first letter in the street name in ascending order (Fig. 1).

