Experiences from the French healthcare system suggest that accreditation risks being reduced to a matter of standardizing practices rather than a matter of improving quality [22]. Therefore, our study primarily focuses on clinically relevant quality indicators relating to the DHQP. The research group scrutinized the standards in the accreditation scheme, and the final list of endpoints was established according to relevant outcomes from a clinical perspective. The direction of changes for some of the chosen outcomes is ambiguous; e.g. polypharmacy can be appropriate in patients with multi-morbidity, but it may also be a result of a lack of treatment plans and medicine reviews. However, according to several national guidelines and systematic reviews, polypharmacy should be reduced, especially among the elderly.

Because the accreditation scheme is mandatory for all Danish GPs, the results are expected to be representative for the effects of accreditation in Danish general practice. Extrapolation to other countries requires further consideration due to differences in the organization of healthcare systems and cultural factors.

The Danish GPs have been informed about the forthcoming accreditation at least 12 months ahead. It may be assumed that some practices will prepare their accreditation in good time as part of their practice development work. Further, some spillover effects must be expected from practices undergoing accreditation to practices awaiting accreditation. Therefore, we collect baseline data from the first half of 2014, and leave out the 2017 population in our analysis.

The GPs allocated to the three clusters did not differ statistically significantly in gender, practice type or region. Therefore, we assume that eventual changes in performance cannot be ascribed to selection.

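### The outcomes are changes from 2014 to 2017, but the plan does not say how change enters the model; adjusting the 2017 value for the practice's 2014 value and for region would settle this at almost no cost.

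*Protocol article*

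**What the plan says.** All points are in the protocol article.

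- **Primary outcome:** the endpoint is "the changes in number of prescribed drugs in patients older than 65 years between the baseline and follow-up period". The sections on secondary outcomes and mortality also express those outcomes as changes between the two periods.
- **Statistics:** "Linear regression will be used for continuously valued outcomes". Logistic regression is used for binary outcomes, among them "changes in proportion of practices with reported adverse events and changes in proportion of practices with a patient satisfaction survey". GEE handles patients clustered in practices. No covariate is named, for or against.
- **Table 2:** the adverse-event variable is yes or no per practice in the period, and the survey outcome is whether a survey was carried out in the period.
- **Randomization:** municipalities were drawn by lot within region: "Within each of the five Danish regions, one-third of the practices within the municipalities that were drawn first were allocated to accreditation in 2016".
- **Power calculation:** a t test compares two means, 6.59 and 6.13, using a cross-sectional SD and no correlation between the years.
- **Discussion:** GPs did not differ significantly in gender, practice type or region. The text continues: "Therefore, we assume that eventual changes in performance cannot be ascribed to selection".

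**The concern.** Three different analyses fit this text: a difference per patient, a difference per practice, and a group-by-period term on two cross-sections. They differ in variance and, for the first, in who is analysed. The power calculation implies a fourth, a comparison of follow-up means alone. A reader cannot tell which will produce the primary result.

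A change in a proportion of practices is a summary over practices. It is not a yes/no response of one practice, so it cannot literally be the dependent variable of a logistic regression.

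The draw was stratified by region, and the text gives no sign that the analysis uses this. The Discussion instead rests on significance tests of GP characteristics. Those tests cover no patient characteristic and no outcome, and region was spread evenly by design, so its balance says little about selection.

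At stake are the definition of the primary estimate, some precision, and a claim about selection that the evidence does not carry.

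**Working it through.** **Inputs from the article.** Practices 604 and 648; patients over 65 per practice m = 584 (SD 378); SD of prescriptions 5.04; ICC 0.2; 5% level (taken as two-sided); power 80%, so the multiplier is 1.960 + 0.842 = 2.802.

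**Assumptions.** The correlation r between a practice's 2014 and 2017 means is not given; 0.5, 0.7 and 0.9 are used. Variance is taken as equal in both years. Practice level is the relevant level: with ICC 0.2 and 584 patients, the between-practice share of the variance of a practice mean is 0.2/(0.2 + 0.8/584) = 99%.

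**Step 1: the article's own figure.** It states a detectable difference of 6.59 − 6.13 = 0.46.
- Equal clusters: design effect 1 + 583 × 0.2 = 117.6. SE = 5.04 × √117.6 × √(1/(604 × 584) + 1/(648 × 584)) = 0.128. Detectable difference 2.802 × 0.128 = 0.358.
- Unequal clusters: CV = 378/584 = 0.647. Design effect 1 + ((1 + 0.647²) × 584 − 1) × 0.2 = 166.5. SE = 0.152. Detectable difference 0.426.

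Neither gives 0.46, which is conservative on its own inputs. The unequal-cluster value is the starting point below.

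**Step 2: three analyses of the same data.** Relative variances are 1 for follow-up only, 2(1 − r) for a change score, and 1 − r² for baseline adjustment. The SE ratio of adjustment to change score is √((1 + r)/2). Each detectable difference is 0.426 times the square root of the relative variance.

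| r (assumed) | Follow-up only | Change score | Adjusted for 2014 | SE ratio, adjusted/change |
|---|---|---|---|---|
| 0.5 | 0.426 | 0.426 | 0.369 | 0.866 |
| 0.7 | 0.426 | 0.330 | 0.305 | 0.922 |
| 0.9 | 0.426 | 0.191 | 0.186 | 0.975 |

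The differences are on the scale of the power calculation (prescriptions over a full year). The ratios do not depend on that scale. The SEs treat practices as independent, as the power calculation does.

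**Step 3: chance imbalance at baseline.** Take a typical imbalance D of one SE, 0.152. Given D, a follow-up-only comparison is shifted by rD: 0.076, 0.107 or 0.137 for r = 0.5, 0.7 or 0.9. A change score is shifted by −(1 − r)D: −0.076, −0.046 or −0.015. Adjustment for the 2014 value leaves none on average.

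**Step 4: region.** If region explains a share q of the variance of practice means, the SE is multiplied by √(1 − q). For an assumed q of 1% to 20%, 0.426 becomes 0.424 to 0.381. Table 1 shows the regions already balanced, for example 28% against 30% in the Capital region and 23% against 23% in Southern Denmark.

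**Step 5: the binary outcomes.** Statistics names a change in a proportion of practices as the response; Table 2 names a yes/no status per practice and period. Only the second can enter a logistic model. Taking 2017 status as the response and 2014 status as a covariate makes the two agree.

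**The case against.** The strongest reply is that this is a condensed article. It is silent on covariates, and such lists commonly sit in a SAP that is not shown. That is correct. A reader might infer that the plan leaves out the baseline and region; the text does not say so.

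Other tempting readings also go too far:

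- **Baseline imbalance is left uncorrected.** A change analysis uses the 2014 data and removes the imbalance apart from regression to the mean (Step 3).
- **The detectable difference would fall from about 0.43 to 0.37, 0.30 or 0.19.** That compares adjustment with follow-up values alone. The article does not define its outcome that way, although its power calculation is built like that.
- **The analysis conditions on survival and drops people who turn 65 after 2014.** This follows only if change is taken per patient, which is not stated. A group-by-period model on two cross-sections fits the text as well and loses nobody.
- **The logistic model is impossible.** Table 2 supplies valid yes/no variables, so the fault is in the wording of the Statistics section.
- **Region terms would correct imbalance between municipalities.** They cannot do so within a region. "Time for accreditation of the practices in the 98 municipalities in Denmark was determined in a randomized lots drawing", so the number drawn was not very small either.

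It is also fair to say that change scores and baseline adjustment are both valid under randomization, that adjusted odds ratios are conditional and need not be more precise, and that outcome data could not be retrieved for balance checks before autumn 2017. What remains is the unstated form of the model, the mis-stated logistic response, a modest efficiency gain and the unsupported inference in the Discussion.

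**Conclusion.** The point holds as a matter of specification and modest efficiency. The article fixes the outcome as a change without saying how the model represents it, and it words two practice-level responses in a form that logistic regression cannot take. It also treats non-significant GP comparisons as evidence against selection, which they cannot provide.

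For continuous outcomes, adjusting for the practice's 2014 value lowers the large-sample SE by about 13%, 8% or 3% against an unadjusted change score, for r of 0.5, 0.7 or 0.9. If practice prescribing is very stable the gain is small. It is larger only against a follow-up-only comparison. These sizes rest on the assumed r, on equal variance in both years, and on the analysis being otherwise unadjusted, which the article leaves open. Region adjustment matches the draw and may add precision. Nothing here shows the planned comparison to be biased.

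**What to change.** State one model in the Statistics section:

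- **Patient-level outcomes:** the 2017 value in all eligible patients listed at follow-up, regressed on arm, region (five levels) and the practice's 2014 mean or proportion for the same outcome. Use the identity link for continuous outcomes and the logit link for binary ones. Keep GEE with robust standard errors.
- **Practice-level outcomes:** the practice's yes/no status in 2017, on arm, region and its 2014 status, with a logit link. Replace the wording about changes in a proportion.
- **Discussion:** delete the inference that selection can be dismissed, and let the baseline table describe the arms.

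Using the practice's 2014 value also means that no patient has to be present in both years. The cost is wording: the 2014 data are already due for retrieval, and the article says that access starts only in autumn 2017, so the model can be fixed before outcomes are seen. Two small items remain. Practices without 2014 data need a simple rule set in advance, and the odds ratios should be reported as conditional on the covariates.

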### Power calculation

The mean number of Danes older than 65 years allocated to an average practice is 584 (standard deviation (SD) 378; registry data at the start of 2015). The mean number of redeemed prescriptions per patient among Danes older than 65 years is 6.59 (SD 5.04; registry data over the full year 2014). For the power calculation, the intra-class correlation (ICC) is set relatively high at 0.2.

Using the formulae in Hemming et al. [19], we are able with our data to detect a difference from a mean number of prescriptions of 6.59 in the control group to 6.13 in the accreditation group using a *t* test with a 5% level of significance accounting for clustering within practices with a power of 80%.

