**Methods/design:**

The study is conducted as a cluster-randomized controlled trial among 1252 practices (clusters) with 2211 general practitioners in Denmark. Practices allocated to accreditation in 2016 serve as the intervention group, and practices allocated to accreditation in 2018 serve as controls. The selected outcomes should meet the following criteria: (1) a high degree of clinical relevance; (2) the possibility to assess changes due to accreditation; (3) availability of data from registers with no self-reporting data. The primary outcome is the number of prescribed drugs in patients older than 65 years. Secondary outcomes are changes in outcomes related to other perspectives of safe medication, good clinical practice and mortality. All outcomes relate to quality indicators included in the Danish Healthcare Quality Program, which is based on general principles for accreditation.

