**Fig. 1 Fig1:**
[figure not shown]
Trial flow for accreditation in general practice (AKIAP)

This randomization allows for comparisons between early accredited practices (2016, *n* = 604 practices) and late accredited practices (2018, *n* = 648 practices) in 2017. Every practice is considered a cluster, which means that there are 1252 clusters in the study. The CRCT study is designed to comply with the recommendations of the CONSORT statement: extension to cluster-randomized trials [12] and SPIRIT.

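### The stated 80% power is for a difference in mean level, while the primary outcome is the 2014-to-2017 change, so 0.46 is not the detectable difference of the primary contrast

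*Protocol article*

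**What the plan says.** The Primary outcome section of the protocol article defines the endpoint as a change: "The primary outcome is the changes in number of prescribed drugs in patients older than 65 years between the baseline and follow-up period". Table 2 (under Clinical outcomes) and the opening of the Discussion also speak of changes. The Data collecting periods section fixes the two windows: "Baseline data are collected from 1 January 2014 to 30 June 2014" and "Follow-up data are collected from 1 January 2017 to 30 June 2017". Data sources says how the count is taken at each time, as the "number of pharmaceutical groups through which an individual redeemed prescriptions on 30 June in the years 2014 and 2017".

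The Power calculation section treats a different comparison. It starts from a mean of "6.59 (SD 5.04; registry data over the full year 2014" and assumes an ICC of 0.2 and a mean of 584 older patients per practice (SD 378). From these it concludes that the trial is able "to detect a difference from a mean number of prescriptions of 6.59 in the control group to 6.13 in the accreditation group using a" two-sample t test, with 80% power at the 5% level, allowing for clustering.

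The Abstract words the endpoint as a level: "The primary outcome is the number of prescribed drugs in patients older than 65 years". The Statistics section names linear regression with GEE for the number of drugs and does not say whether the 2014 value enters as a subtraction, a covariate or a period-by-group term.

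**The concern.** A t test of 6.59 against 6.13 with a one-year between-person SD and one ICC describes two mean levels at one time. The variance of a between-arm difference in change also depends on how closely a practice's 2014 mean predicts its 2017 mean. The power paragraph has no SD of change, no between-period correlation and no baseline adjustment, so its inputs cannot give the precision of the primary contrast.

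The omission is not a detail at the plan's own ICC. The between-practice variance is about 5.08, while patient-level variation adds only about 0.035 to the variance of a practice mean. The missing correlation therefore fixes the precision almost alone.

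At stake is how the result is read. A reader of a null result would take 0.46 as the limit of what the trial could detect. If practices' prescribing levels persist over time, the true limit could be half that or less. If they do not persist and a raw change score is analysed, the limit is larger.

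**Working it through.** **Inputs.** From Participants and study design: 604 and 648 practices. From Power calculation: mean practice size 584, SD 378; SD of the count 5.04; ICC 0.2; 5% level; 80% power. Assumptions: the test is two-sided (not stated); practices are the clusters, as in the plan; variances are equal in the two periods; r, the between-period correlation of practice means, is not in the document and is varied.

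**Constants.** z = 1.960 + 0.842 = 2.802. CV of practice size = 378/584 = 0.647, so 1 + CV² = 1.419. SD² = 25.40. 1/604 + 1/648 = 0.003199. Stated difference = 6.59 − 6.13 = 0.46.

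**1. The plan's own (level) comparison.**
- Unequal sizes: design effect = 1 + (1.419 × 584 − 1) × 0.2 = 166.5. Variance per practice = 25.40 × 166.5/584 = 7.243. SE = √(7.243 × 0.003199) = 0.152. Detectable difference = 2.802 × 0.152 = **0.426**. Power for 0.46 = 85.6%.
- Equal sizes: design effect = 1 + 583 × 0.2 = 117.6. Detectable difference = **0.358**. Power for 0.46 = 94.9%.

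Neither gives exactly 0.46 at 80%. The claim holds for a level comparison in the sense of at least 80% power.

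**2. Unadjusted change score.** Between-practice variance = 0.2 × 25.40 = 5.08; within-practice = 20.32. Variance of a practice's change, unequal sizes:

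2 × 5.08 × (1 − r) × 1.419 + 2 × 20.32/584 = 14.42(1 − r) + 0.070

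Detectable difference = 2.802 × √(variance × 0.003199).

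**3. 2017 value adjusted for the 2014 practice mean.** Level variance times (1 − r²), so detectable difference = 0.426 × √(1 − r²).

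| r (assumed) | Change score: detectable difference | Change score: power for 0.46 | Baseline-adjusted: detectable difference |
|---|---|---|---|
| 0 | 0.60 | 57% | 0.43 |
| 0.2 | 0.54 | 67% | 0.42 |
| 0.5 | 0.43 | 85% | 0.37 |
| 0.8 | 0.27 | over 99% | 0.26 |
| 0.9 | 0.20 | over 99% | 0.19 |

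Step 2 treats patient-level noise as independent between periods. If r is instead applied to the whole variance of the practice mean, the factor is 2(1 − r) and the change-score figure at r = 0.9 is 0.191 rather than 0.195. Nothing else moves materially. With equal sizes the change-score figures are 0.51 (r = 0), 0.36 (r = 0.5) and 0.17 (r = 0.9).

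**4. Break-even for 0.46 at 80%.** Largest allowed variance = (0.46/2.802)²/0.003199 = 8.43. With unequal sizes, 1 − r = (8.43 − 0.07)/14.42 = 0.58, so r ≈ **0.42**. With equal sizes the coefficient is 2 × 5.08 = 10.16 and r ≈ **0.18**.

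**The case against.** The strongest reply is that nothing material is lost. Under randomisation the expected between-arm difference in change equals the expected difference in 2017 level, so 0.46 is an effect on the right scale and only its variance is approximated. Leaving out the baseline correlation is a common planning simplification and often errs on the safe side. This stands.

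A reader might infer from the 57% and 67% in the table that the trial is underpowered. The document does not support that. Those figures need an unadjusted change score, which the Statistics section does not specify, together with a low r. They also hold the ICC at 0.2, which the plan itself says is deliberately high. Even at r = 0, an ICC of about 0.116 brings the change-score figure back to 0.46: the design effect is 1 + (1.419 × 584 − 1) × 0.116 = 97.0, and 2.802 × √(2 × 25.40 × 97.0/584 × 0.003199) = 0.46. Practices that differ greatly in level but show no persistence over time would be an extreme combination.

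A reader might also see a rival definition of the outcome in the Randomization section, where "This randomization allows for comparisons between early accredited practices" and late accredited ones are said to be compared in 2017. That sentence gives the timing of the comparison and does not exclude a baseline, so it is no contradiction. The Abstract's level wording is a condensed statement and a mild inconsistency only.

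Finally, group sizes were set by the accreditation body, so no design decision turns on the figure. That limits the consequence, but the power sentence still describes a contrast other than the stated primary one.

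**Conclusion.** The point holds in a limited form. The power paragraph gives the precision of a comparison of mean levels. It does not give the precision of the 2014-to-2017 change that the protocol names as primary, because the between-period correlation is absent. Depending on r and on how the 2014 value is used, the detectable difference lies anywhere from about 0.60 to 0.19, against the stated 0.46.

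The direction of the error is unknown. An unadjusted change score has at least 80% power for 0.46 only if r is about 0.42 or more (about 0.18 with equal practice sizes). A baseline-adjusted analysis reaches it at every r, so the published figure may well be conservative.

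These results rest on the plan's SD, ICC, practice sizes and choice of the practice as cluster, on a two-sided test, and on assumed values of r. Whether full-year prescription data suit an endpoint counted at 30 June is a separate question and is not needed here. The correction should be made, but it does not threaten the trial.

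**What to change.** Name one primary contrast. The 2017 count adjusted for the 2014 value is preferable: the 2014 data are already part of the plan, and in these calculations it is never less precise than the level comparison. Use the same wording in the Abstract, Table 2, the Primary outcome section and the Statistics section.

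In the Power calculation section, restate the detectable difference for that contrast. Add r as an explicit input and show a range (for example 0.5, 0.7 and 0.9). Replace the range with a register estimate pooled over arms if access allows. Data sources and Trial status say that the project group may not retrieve data until autumn 2017, so the assumed range may have to serve first.

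The cost is a rewritten power paragraph and, if access permits, one register summary. The figure becomes less favourable only if an unadjusted change score is kept and r proves low. Recruitment and data collection do not change.

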## Methods/design

### Participants and study design

The accreditation scheme in Denmark is rolled out as a cluster-randomized controlled trial (CRCT). All 1922 general practices are eligible for the study and are allocated to undergo accreditation in 2016, 2017 and 2018 respectively. Practices allocated to accreditation in 2016 (accreditation2016) and representing 604 clusters are selected as the intervention group, while practices allocated to accreditation in 2018 (accreditation2018) represent 648 clusters and serve as the control group. Practices are assigned an accreditation date 1 year in advance, and in order to avoid contamination from the intervention group, practices allocated to accreditation in 2017 (accreditation2017), representing 664 practices, will be excluded from analysis.

This design, in addition to the comprehensive Danish National Health registers, offers a unique opportunity to conduct research on the effects of accreditation [6–8]. Moreover, the design makes possible a comparison of practices that have already accomplished accreditation with practices waiting to be accredited [9]. Additionally, the national Civil Registration System (CRS) facilitates the collection of relevant data independent of the involved practices [10].

The Danish healthcare system is tax-financed, and most general practitioners (GPs) and hospital services are free of charge. General practice is characterized by five key components. (1) There is a list system associating citizens with a GP. GPs can close for uptake when they have 1600 persons on the list but are allowed to enroll up to 2550 persons. (2) The GP acts as gatekeeper and first-line provider in the sense that a referral from a GP is required for most office-based specialists and always for inpatient and outpatient hospital treatment. (3) An after-hours system is staffed by GPs on a rotation basis. (4) There is a mixed capitation and fee-for-service system. (5) GPs are self-employed, working on contract for the public funder based on a national agreement that details not only services and reimbursement but also opening hours and required postgraduate education [11]. Danish general practice constitutes 1922 practices comprising a total of 3329 GPs.

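### The stated 0.46-prescription difference at 80% power does not follow from the printed inputs, which give about 0.43 at 80% or about 86% power for 0.46

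*Protocol article*

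**What the plan says.** The Power calculation section of the protocol article gives both inputs and result. On practice size it states: "The mean number of Danes older than 65 years allocated to an average practice is 584 (standard deviation (SD) 378; registry data at the start". For the outcome, the average count of redeemed items in this age group "is 6.59 (SD 5.04; registry data over the full year 2014". The clustering assumption is that "the intra-class correlation (ICC) is set relatively high at 0.2".

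Citing published formulae, the section concludes that the study can "detect a difference from a mean number of prescriptions of 6.59 in the control group to 6.13 in the accreditation group". It specifies a *t* test at 5% and describes the calculation as "accounting for clustering within practices with a power of 80" per cent.

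The section does not repeat the number of practices. Participants and study design gives it for the accreditation arm, "representing 604 clusters are selected as the intervention group", with 648 for the control arm. Randomization repeats both figures: "early accredited practices (2016, *n* = 604 practices) and late accredited practices (2018, *n* = 648 practices"). No loss of practices, covariate adjustment or other allowance is stated for the power calculation.

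**The concern.** The inputs needed for a two-arm parallel cluster calculation are printed, except the sidedness of the test, so the result can be checked. It does not come out as stated.

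This is the only statement of what the trial can detect on its primary outcome, and a null result may be read against it. A reader who tries to reproduce it cannot tell whether the formula was misapplied or whether the ICC, the handling of unequal practice sizes or the number of practices differs from what is printed.

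**Working it through.** **Inputs.**
- Mean practice size m = 584, SD 378, so CV = 378/584 = 0.647 and CV² = 0.419 (Power calculation).
- Outcome SD = 5.04, ICC = 0.2, level 5%, power 80% (Power calculation).
- Practices: 604 and 648 (Participants and study design; Randomization).
- Assumption: a two-sided test, since sidedness is not stated. The multiplier is 1.960 + 0.842 = 2.802.

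**Formulae.** With design effect DE,

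SE = √[ SD² × DE/m × (1/604 + 1/648) ], and detectable difference = 2.802 × SE.

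The term 1/604 + 1/648 equals 0.003199.

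**Step 1: the plan's own figure.** The stated difference is 6.59 − 6.13 = 0.46. It is recovered at 5% and 80% if CV is used without squaring:

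- DE = 1 + ((1 + 0.647) × 584 − 1) × 0.2 = 1 + (962 − 1) × 0.2 = 193.2
- SE = √(25.40 × 193.2/584 × 0.003199) = 0.164
- Difference = 2.802 × 0.164 = 0.459, that is, 6.59 to 6.13
- Power at 0.46 = Φ(0.46/0.164 − 1.960) = 80.1%

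**Step 2: the standard design effect for unequal clusters**, in which CV is squared:

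- DE = 1 + ((1 + 0.419) × 584 − 1) × 0.2 = 166.5
- SE = √(25.40 × 166.5/584 × 0.003199) = 0.152
- Difference = 2.802 × 0.152 = 0.426, that is, 6.59 to 6.16
- Power at 0.46 = Φ(0.46/0.152 − 1.960) = 85.6%

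**Step 3: does an ordinary variant of Step 2 explain the gap?**

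| Variant (CV squared) | Detectable difference at 80% |
|---|---|
| *t* quantiles instead of normal | 0.427 |
| 604 practices in both arms | 0.434 |
| One-sided 5% | 0.379 |
| 5.04 read as the within-practice SD | 0.477 |

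None gives 0.46. Rounding does not either: for differences from 0.455 to 0.465, power runs from 84.8% to 86.3%.

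**Step 4: what would have to change to reach 0.46.** With CV squared and everything else as printed, any one of these would do: an ICC of about 0.233, about 537 practices per arm, or an outcome SD of about 5.44. Alternatively, power of 85% gives 0.456, which also rounds to 6.13. The document states none of these values.

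**Size of the discrepancy.** 0.46 − 0.426 = 0.034 prescriptions; 0.46/0.426 = 1.08, so the difference is overstated by about 8%. Power is understated by 85.6 − 80 = 5.6 points.

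**The case against.** The best defence is that the sentence remains true as a lower bound: if 0.43 is detectable with 80% power, 0.46 is detectable with at least 80%. Group sizes were set by the accrediting institute and not derived from this calculation, so no recruitment, analysis or stopping decision depends on it. A null result would in any case be judged mainly on its confidence interval. All of this stands, and it limits the weight of the point. But the text pairs 0.46 with 80% and does not say "at least".

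Secondly, some inputs could differ from those used here. The ICC is printed to one decimal; values from 0.15 to 0.25 give differences of about 0.37 to 0.48, which includes 0.46. The section does not say how many practices entered the calculation, and the cited formulae are not at hand. These are possible explanations. However, an ICC described as set at 0.2 reads as an exact choice, and no other practice count is given. If one of them is the reason, printing it settles the matter.

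Three stronger readings are tempting and are not supported:
- A reader might assume equal practice sizes, obtain 0.358 (94.9% power at 0.46), and call the figure far off. The section prints an SD of 378 for practice size, so that calculation ignores a stated input.
- A reader might infer that the trial is underpowered. The error runs the other way.
- A reader might ask for a municipality-based figure here, because lots were drawn by municipality. That is a separate design question, and it needs a municipality-level ICC that the document does not give.

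**Conclusion.** The stated pair of 0.46 and 80% does not follow from the article's own inputs. With practice as the cluster, the printed variation in practice size, an ICC of exactly 0.2, all 1252 practices and a two-sided 5% test, the figures are about 0.43 at 80% power or about 86% power for 0.46. A one-sided test would widen the mismatch.

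The unsquared CV reproduces both the difference and the power, which makes it a plausible cause. It remains an inference, because the working is not shown and a nominal power of 85% would also round to 6.13. This is a minor but definite error in a reported figure, in the conservative direction, and it has no consequence for the conduct of the trial.

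**What to change.** Replace the closing sentence of the Power calculation section with one of two statements: that 80% power corresponds to a difference of about 0.43 prescriptions (6.59 to 6.16), with practice as cluster and a CV of practice size of 0.65; or that power for a difference of 0.46 is about 86%. State in the same sentence the design effect, the number of practices per arm and that the test is two-sided.

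If a different ICC, another handling of unequal practice sizes, another power level or fewer practices was used, keep 0.46 and print that input. The cost is one recalculated sentence, with no change to the design, data or analysis.
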